#### Primary and Secondary Outcomes

The primary and secondary outcome variables will be assessed at the baseline, postworkshop, and follow-up time points. A chi-square test will be used to assess if there are any differences between the intervention group and waitlist control at baseline. A 2-way repeated measures ANOVA will be conducted to compare the means between the intervention group and waitlist control group (between-subjects factor) over the 3 time points (within-subjects factor) for each of the primary and secondary variables. This analysis will be run to test for any time through conditional interactions. Demographics, such as age, gender, role of dietitian, and consultation delivery mode, will be included as covariates in the analysis. Multiple regression analyses will be used to determine whether changes (residual) in capability, opportunity, motivation, and health professional preparedness predict changes in behavior (range of use or frequency of use) at each of the 3 time points (while controlling for baseline behavior).

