### Outcomes

The primary outcome of this study will be behavior change, which will be operationalized in 2 ways for dietetic practice. These outcomes include (1) a change in the number of behavior change techniques used and (2) a change in the frequency of behavior change techniques used. This change will be measured across the 3 time points. While this may not be an absolute measure of behavior change technique delivery, however, any change will capture the range of techniques taken from the workshops, which may be more indicative of the dietitians’ understanding and application of the COM-B model. To further capture the uniqueness of the behavior change techniques delivered by dietitians, the type of technique will also be measured across the 3 time points. Secondary outcomes include changes in perceived capability, opportunity, motivation, and preparedness as a health professional toward delivering behavior change techniques.

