### Measures

Behavior will be measured with two items to determine (1) the use of behavior change techniques and (2) the frequency of use. The first item asks participants “Which of the following behavior change techniques do you use in practice?” Participants will indicate which of the 14 techniques they have used by rating their answer as either yes, no, or unsure. A total of 14 techniques were chosen based upon techniques used for dietary behavior change in the literature [31], as well as consultations with an advisory group of dietitians to determine the appropriateness and practicality of the techniques. A composite score will be calculated to determine the number of techniques used. A second item will also be included to identify how frequently dietitians use these techniques in practice, for example, “How often do you currently use behavior change techniques when interacting with clients?” Participants will rate this item on a 5-point Likert scale from never (0) to always (4).

Capability, opportunity, and motivation will be measured using the COM-B questionnaire [38], which has been adapted for delivering behavior change techniques when interacting with clients in health contexts. This measure includes 6 items and 6 domains that reflect each component of the COM-B model as outlined by Michie et al [13]. Participants will rate their level of agreement with each item on an 11-point scale, with items ranging from strongly disagree (0) to strongly agree (10). An example item includes “I have the PHYSICAL opportunity to deliver behavior change techniques when interacting with clients (eg, time, the necessary materials, reminders, and space).”

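### The arm comparison treats the baseline score as an outcome level instead of adjusting for it, and the two primary measures have no stated success rule

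*Protocol article*

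**What the plan says.** Under Outcomes: "The primary outcome of this study will be behavior change, which will be operationalized in 2 ways for dietetic practice". The two measures are the number of techniques used and how often they are used. No visit is singled out: "This change will be measured across the 3 time points".

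Under Primary and Secondary Outcomes, the model is described as "A 2-way repeated measures ANOVA will be conducted to compare the means between the intervention group and waitlist control group", "over the 3 time points (within-subjects factor) for each of the primary and secondary variables". Its purpose: "This analysis will be run to test for any time through conditional interactions". I read this as the time-by-condition interaction. The covariates listed are age, gender, role and consultation mode. The baseline value of the outcome is not among them. It is controlled only in the regressions of behavior change on changes in capability, opportunity, motivation and preparedness.

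Under Participants, the trial is sized for a single test at α = .05 with 80% power, 42 per group. Under Study Design and Procedure, the first post-baseline questionnaire follows directly after the second workshop.

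**The concern.** Baseline comes before any training, so any arm difference there is chance. An ANOVA that carries baseline as an outcome level estimates that difference as if it were unknown. A model with baseline as a covariate uses the same data and removes the variance that baseline explains. At stake is power in a trial that expects heavy attrition.

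The second issue is what a significant interaction means. The behavior item asks "Which of the following behavior change techniques do you use in practice". At the questionnaire straight after workshop 2, the nine techniques introduced there cannot yet have been used with clients as a result of that session. The 2-df test gives that reading the same weight as the 3-month one. If the arm difference is not reported by visit, a positive result could rest on the immediate reading without anyone noticing.

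The third issue is separate from the model. With two primary measures and no statement of whether either or both must succeed, the overall error rate is undefined.

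**Working it through.** **The plan's own figure.** The stated inputs are an effect of 0.2 (read here as Cohen's f, an assumption), df 1 and 82, power .80, α .05 and total N = 84.
- One-way test with df 1 and 82: λ = 0.2² × 84 = 3.36, power 44%.
- Three-visit interaction at ρ = 0: λ = 0.2² × 84 × 3/(1 − 0) = 10.08 with df 2 and 164, power 81%.

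So 84 is approached for the planned interaction only at an unstated correlation of zero, and with degrees of freedom other than those printed. The plan therefore supplies neither ρ nor an effect in SD units, and both are assumed below.

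**Assumptions.** 1:1 allocation, compound symmetry with correlation ρ, arm differences (0, d₁, d₂) in SD units at baseline, postworkshop and 3 months with mean v̄, controls untrained at the visits compared, and demographic covariates ignored in every test.

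**Formulas (noncentral F).**
- Planned interaction: λ = (N/4) Σ(v − v̄)²/(1 − ρ), df 2 and 2(N − 2).
- Joint test of both later visits adjusted for baseline: λ = planned λ + (N/4) × 3v̄²/(1 + 2ρ), df 2 and 2(N − 3). The added term is never negative.
- 3-month contrast alone, adjusted for baseline: λ = (N/4) d₂²/(1 − ρ²), df 1 and N − 3.

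**Example: N = 84, ρ = 0.5, d₁ = d₂ = 0.5, so v̄ = 1/3.**
- Planned: 21 × 0.25 × (2/3)/0.5 = 7.0, power 65%.
- Joint, adjusted: 7.0 + 21 × 3 × (1/9)/2 = 10.5, power 83%.
- 3 months only: 21 × 0.25/0.75 = 7.0 on 1 df, power 74%.

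**Power for a sustained 0.5 SD effect.**

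| N | ρ | Planned | Joint, adjusted | 3 months only |
|---|---|---|---|---|
| 84 | 0.3 | 50% | 78% | 66% |
| 84 | 0.5 | 65% | 83% | 74% |
| 84 | 0.7 | 87% | 93% | 89% |
| 70 | 0.3 | 42% | 70% | 58% |
| 70 | 0.5 | 56% | 75% | 66% |
| 70 | 0.7 | 79% | 88% | 82% |

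The 70 rows are the completers left by 140 recruits and 50% attrition. For a sustained effect the ratio of adjusted to planned λ is 3/(1 + 2ρ). At ρ = 0.9 it is 3/2.8 = 1.07 and all the tests exceed 99% power at N = 84.

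**If the effect does not last (N = 84, ρ = 0.5).**
- 0.5 SD then 0.25 SD: planned 52%, joint adjusted 66%, 3 months only 26%.
- 0.5 SD then nothing: planned 65%, the same as for a sustained effect; joint adjusted 70%.

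Neither joint test tells a momentary change in answers from a lasting one. Only the arm difference by visit does.

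**Two primary measures, success on either.** 1 − 0.95² = 9.75% if independent. For a bivariate normal pair it is 9.1% at correlation 0.5 and 7.0% at 0.9.

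**The case against.** The stated objective is change across three time points, and a group-by-time interaction answers it. That stands, and it is why the change proposed here keeps both later visits. Adjusting a later value for baseline gives the same arm difference as adjusting the change score for baseline, so the objective is not altered.

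A reader might infer that the planned ANOVA loses error control. It does not: the interaction test holds its 5% level if sphericity holds, and replacing it with ANCOVA would leave the 9.75% untouched. That figure comes from having two measures and needs an either-suffices rule. If both must succeed there is no inflation, and an analysis plan not shown may state the rule.

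A reader might also infer that a single 3-month contrast should replace the interaction because the interaction has lower power in general. The protocol does not support that. The 3-month contrast wins only for a sustained effect and ρ below about 0.8, and it loses clearly if the effect halves. Nor is the immediate reading empty: workshop 1 already covers four techniques, and the gap between workshops is not stated.

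The strongest objection concerns the control arm. Waitlist participants are offered workshops in 3 months, yet both groups are said to answer questionnaires after their second workshop and at 3 months, and waitlist postworkshop data enter the data set. Read literally, controls could be trained at both later visits. Figure 1 may settle this but is not shown. The ambiguity affects the planned ANOVA as much as any replacement.

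The baseline check ("A chi-square test will be used to assess if there are any differences between the intervention group and waitlist control at baseline") is a minor side point. A chi-square test suits gender, role and delivery mode, but not age in years or a 0–14 score, and nothing above depends on it.

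**Conclusion.** The point holds in this form: the group comparison uses baseline as an outcome level where it should be a covariate, and this gives up power for nothing. Under the stated assumptions the gain from adjustment at 84 completers is 28, 18 and 6 percentage points at ρ of 0.3, 0.5 and 0.7, and nil near 0.9. Noncentrality is never lower under adjustment, whether or not the effect fades. The size of the gain rests on an assumed effect, correlation and compound symmetry.

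The multiplicity point is separate and conditional: up to 9.75% familywise error if either measure can carry the claim. Both points presuppose that the control arm is untrained at the visits compared, which the article leaves unclear. This is a recommended improvement, not a flaw that invalidates the trial.

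**What to change.** 1. First reconcile Study Design and Procedure so that it states, for each arm, when each questionnaire falls relative to that arm's own workshops.
2. Analyse the postworkshop and 3-month values as outcomes, with the baseline value of the same outcome and the listed demographics as covariates (ANCOVA or a baseline-adjusted repeated measures model). Report the arm difference with its confidence interval at each visit.
3. State the success rule. A fixed order would control the error rate: number of techniques at 5%, then frequency at 5% only if the first is significant.
4. Restate the sample size for the test chosen, with its effect and correlation.
5. Optionally, replace the chi-square check with a descriptive baseline table.

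No new visits or data are needed. The cost of the fixed order is that frequency cannot be claimed if the first test fails. The sample size paragraph has to be redone, and because recruitment began in June 2023 the change should be dated and made before outcomes are examined by arm.

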#### Qualitative Data

Interview data will be analyzed using thematic analysis to identify common themes concerning the impact of the intervention (eg, barriers or enablers experienced in practice) and to inform the acceptability and feasibility of the workshops [45].

### Ethical Considerations

Ethics approval was granted for this study by the Human Research Ethics Office on January 20, 2023 (HRE2023-0026). This project has also been approved by the Human Research Ethics Committee (HRE2023-0026) and the Australian and New Zealand Clinical Trials Registry (ACTRN12623000525684). Informed consent to participate in the study will be received during the initial recruitment stage before any data collection. Dietitians who are interested in participating will follow a Qualtrics survey link to the participant information sheet that details their involvement in the trial. Following this information, participants will be asked to consent to participate in the study, and if they choose to withdraw from the study, they will also consent to being contacted with follow-up questions. The workshops provided will be freely accessible and are able to be recorded as continuous professional development under Dietitians Australia.

### Research Data Plans

All research data collected as part of this project will be stored on the research drive of the university. Only the research team will have access to this data. Participant data will be collected and matched across the 3 time points based on their name, email address, and participant ID. All the data collected as part of this trial will remain confidential. After data collection, the 3 time points will be matched, and the data will be deidentified. Participants will be sent email reminders for each upcoming workshop and assessment.

## Results

Participant recruitment commenced in June 2023. Recruitment will be staggered over 12 months. Data analysis will commence in 2024, with the anticipated publication of results in 2024.

## Discussion

### Principal Findings

This trial will examine the effectiveness and acceptability of two 2-hour behavior change workshops and, to our knowledge, is the first training workshop to promote behavior change techniques among dietitians. There is evidence to suggest that training health professionals is beneficial in improving capability and motivation for using behavior change techniques in practice [20,33]. It is important that health professionals are confident in eliciting and identifying opportunities to facilitate brief opportunistic interventions with the goal of developing long-term behavioral maintenance. The findings of this study will provide insights into effective strategies for training of allied health professionals, such as dietitians, which could inform efforts to incorporate behavior change education into either formalized training or continuous professional development.

### Strengths and Limitations

A strength of this study is the use of a rigorous, co-designed process involving both experienced researchers in behavior change and a supervisory team of dietitians. Dietitians have been involved throughout the workshop design process and provided feedback to ensure terminology is consistent and information is tailored to nutrition and dietetic practice. Co-design provides valuable insights into stakeholders and consumer perspectives, allowing for a more targeted approach to intervention design [46]. A potential limitation that may arise during the study is that participants who do express interest are likely to have high motivation and potential knowledge of behavior change before the workshops. This may lead to only minor or no changes in capability, opportunity, and motivation, even if the workshops are effective, and may limit the generalizability of conclusions concerning uptake and interest in training.

### Conclusions

The examination of the effectiveness and acceptability of this trial will inform strategies for continuous professional development in behavior change. If found to be effective and acceptable by dietitians, there is potential for future training and professional development programs across allied health professionals who are in opportunistic and client-facing roles to target chronic disease prevention and management [47,48]. Our findings will also contribute to our understanding of translating skills around behavior change techniques into practice with clients and identifying those components of COM where dietitians may need future support.

## Appendix

Multimedia Appendix 1 Behavior change techniques mapped to workshop material.

## Abbreviations

COM-B: Capability, Opportunity, Motivation, and Behavior
CONSORT: Consolidated Standards of Reporting Trials
SPIRIT: Standard Protocol Items: Recommendations for Interventional Trials
